## Methods

### Study Design

The protocol involves a type I hybrid implementation trial design [53], where we pilot test the NP-led iRaPID program. The study is a 2-arm RCT that examines the feasibility and acceptability of the program among people who inject drugs and clinical stakeholders. In the process, we can provide a preliminary estimate of the efficacy of PrEP and MOUD uptake by comparing the iRaPID program against treatment as usual (TAU) among HIV-negative people who inject drugs. We hypothesize that the iRaPID program will be more efficacious than will TAU on PrEP and MOUD uptake and adherence.

In this type I hybrid implementation trial design, we collect process measures to inform future implementation efforts. We will explore potential patient- and provider-level barriers and facilitators of the program regarding its implementation in real-world settings. More specifically, we will assess at both these levels the overall satisfaction, perceived utility, and relevance of each intervention component; determine the relevant needs of the target population (ie, people who inject drugs), thereby delineating intervention characteristics that address those needs; and explore the barriers to implementation of the iRaPID program, such as logistical barriers and time and resource constraints. Finally, changes needed to accommodate same-day coprescription of PrEP and MOUD will be established, along with the resources and structural changes necessary for the successful implementation of the program.

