### Intervention Procedures

#### Treatment as Usual

Participants randomized to the TAU group will follow the existing clinical guidelines to receive PrEP, MOUD, or both medications. They are provided with a comprehensive list of PrEP and MOUD programs available in the area. Since PrEP and MOUD services are not integrated within the current standard of care, participants will have to be screened at separate visits (one for PrEP and another for MOUD) if they are interested in both programs unless they find a prescriber who will provide both.

For PrEP, the current standard of care generally involves 2 clinical appointments. During the first visit, patients are assessed for eligibility and PrEP readiness and receive additional counseling on using PrEP. Additionally, laboratory screenings are ordered. During the second visit, which usually occurs 1 to 3 weeks later, the laboratory results are reviewed, PrEP readiness is reassessed, and the patient is provided with a PrEP prescription that they will need to fill at a pharmacy. Access to MOUD also entails 2 separate clinic visits at least 3 days apart. The first encompasses an eligibility assessment, patient counseling, and an evaluation of the patient's readiness to start therapy. Patients are also given a home induction kit and asked to follow up in 3 days for further counseling on maintenance therapy (Figure 1).

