We will also estimate the preliminary efficacy of PrEP and MOUD uptake in this pilot RCT of the iRaPID intervention versus TAU (primary outcome). This will be determined by assessing PrEP and MOUD uptake (ie, current use). For those who initiate PrEP, we will also evaluate the time to PrEP initiation, along with adherence and persistence on PrEP, as part of the secondary outcome. Time to PrEP initiation will be calculated by recording the number of days between the first encounter with the NP or health care provider and the day of initiation of PrEP, validated by the pharmacy PrEP pick-up date. We will measure PrEP adherence using the visual analog scale [74] and confirm with dried blood spot testing [75-77]. Persistence on PrEP will be measured by assessing pharmacy data, including both refill (if refilled within 30 days after exhausting PrEP from previous fill or not) and pick-up information. Given the importance of moderating factors on the effect of efficacy, we will measure individual (eg, sociodemographic, sexually transmitted infection, drug use, depression), social (eg, social support), and structural (eg, stigma, physician distrust) factors at each in-depth interview.

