### Statistical Analyses

Feasibility will be assessed through the analysis of data collected by the research team, including the number of participants screened and enrolled per month, the proportion of eligible participants who enroll in the study, the treatment-specific proportion of participants completing follow-up visits, rates of adherence to the intervention protocol, and fidelity of implementation measured by the percentage of domains captured by the NPs at each time point. Acceptability analysis will be based on descriptive statistics from the acceptability measures, such as simple means and percentages between treatment arms, and thematic analysis of qualitative data collected in postimplementation focus groups.

Meanwhile, preliminary efficacy analysis will assess the hypothesis that the iRaPID intervention will perform better than TAU over time using a primary outcome (ie, PrEP uptake) and secondary outcomes (ie, time to PrEP initiation, PrEP adherence and persistence). We will first test baseline characteristics for homogeneity between treatment arms using an independent-samples *t* test or Wilcoxon rank sum test (if unequal variances are assessed) for continuous variables and chi-square tests or Fisher exact tests (if any small cell sizes) for categorical variables. This analysis of baseline characteristics will be used to determine significantly different factors to include in the final model for adjustment. To assess our hypotheses relating to preliminary efficacy, we will use a generalized linear mixed model [78] with random subject effects to account for the correlation in repeated measurements that occur within subjects. Treatment assignment, time, and the interaction between time and treatment assignment, including confounders such as sociodemographic characteristics and prior PrEP or MOUD engagement, will be included as covariates. The proportion of participants that initiate PrEP will be estimated and compared using the linear contrast statement in SAS PROC GLIMMIX (SAS Institute). Similar analyses will be conducted for other outcomes, including MOUD uptake, time to PrEP initiation, optimal adherence to PrEP, and PrEP persistence.

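### Secondary PrEP outcomes are compared between arms only among participants who start PrEP, and time to initiation gets a model and a clock that do not suit it

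*Protocol article*

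**What the plan says.** **Population.** The Outcome Measures section of the protocol article sets the group for the secondary PrEP outcomes: "For those who initiate PrEP, we will also evaluate the time to PrEP initiation, along with adherence and persistence on PrEP".

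**Purpose.** Statistical Analyses lists time to initiation, adherence and persistence as secondary outcomes for the hypothesis that iRaPID does better than TAU. Study Design states the hypothesis with adherence in it: "We hypothesize that the iRaPID program will be more efficacious than will TAU on PrEP and MOUD uptake and adherence". Neither section labels these comparisons descriptive.

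**Model.** The efficacy model is a "generalized linear mixed model [78] with random subject effects to account for the correlation in repeated measurements that occur within subjects", with treatment, time and their interaction as covariates. It is then extended: "Similar analyses will be conducted for other outcomes, including MOUD uptake, time to PrEP initiation, optimal adherence to PrEP, and PrEP persistence".

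**Clock.** Time to initiation is the "number of days between the first encounter with the NP or health care provider and the day of initiation of PrEP"; pharmacy pick-up records serve as validation.

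**Routes to PrEP.** In TAU, participants find a provider themselves: "They are provided with a comprehensive list of PrEP and MOUD programs available in the area". The prescription comes at a further appointment: "During the second visit, which usually occurs 1 to 3 weeks later". In iRaPID, the nurse practitioner offers a prescription at the first visit.

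**The concern.** There are two separate faults.

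**Who is compared.** Whether someone starts PrEP is decided after randomisation, and iRaPID exists to change it. TAU starters have found a provider and usually attended twice. iRaPID starters can include people who would not have done so. If the intervention works, the two groups of starters differ in kind, and an adherence or persistence difference between them mixes the effect of iRaPID with that difference in make-up. Adjustment for sociodemographic factors and prior PrEP or MOUD engagement does not restore the balance that randomisation gave.

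**How time is analysed.** Time to initiation has at most one value per person. Random subject effects and a time-by-treatment term are built for repeated values, so the model does not suit it. Leaving out non-starters discards the censored observations, which carry much of the contrast between arms. The clock also starts at the first provider encounter. For TAU that encounter follows randomisation by an unknown interval and may never happen.

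The trial is meant to supply estimates for a future RCT. A misleading adherence, persistence or timing estimate would pass into that design.

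**Working it through.** The article states no expected uptake, adherence or persistence rate, so there is no planned figure to reproduce for these outcomes. Every rate below is an assumption, varied over a range.

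**Inputs from the article:** 50 participants allocated 1:1, so about 25 per arm; follow-up to 6 months (taken as 180 days); TAU prescription 1 to 3 weeks after the first visit (midpoint 14 days).

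**1. Adherence: formulas.** Let pT and pI be the proportions starting in TAU and iRaPID. Everyone who would start under TAU is assumed also to start under iRaPID (always-starters, adherence aA). The rest of the iRaPID starters are extra starters (adherence aN). If iRaPID does not change adherence in always-starters:

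- starters-only difference = [(pI − pT)/pI] × (aN − aA)
- all-randomised difference, with non-starters counted as not adherent = (pI − pT) × aN

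The first depends on how the extra starters compare with the always-starters. It is zero when aN = aA, negative when aN is lower and positive when aN is higher.

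**2. Base case.** Assume pT = 20%, pI = 60%, aA = 80%, aN = 50%.

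| Comparison | iRaPID | TAU | Difference |
|---|---|---|---|
| Starters only | (0.2 × 0.8 + 0.4 × 0.5)/0.6 = 60% | 80% | −20 points |
| All randomised | 0.2 × 0.8 + 0.4 × 0.5 = 36% | 0.2 × 0.8 = 16% | +20 points |

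**3. Range.** This covers 27 combinations: pT 10 to 30%, pI 40 to 80%, aA 80%, aN 30 to 70%. In all of them the extra starters adhere less well.

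- No effect on always-starters: the starters-only difference is negative in all 27 (−2.5 to −43.8 points), and the all-randomised difference is positive in all 27 (+3 to +49 points).
- A true gain of 10 points in always-starters: the starters-only difference is still negative in 23, zero in 3 and positive in 1.

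**4. Simulation.** 20,000 trials were run with 25 per arm.

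- Base case: the starters-only estimate falls below zero in 80% of trials, with a median of 5 TAU starters. The all-randomised estimate does so in 3.6%.
- Same uptake, but 65% adherence in both kinds of starter: the starters-only difference averages 0.

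**5. Time to initiation.** Assume uptake of 60% v 20%, TAU starters at day 14, and iRaPID starters 75% at a mean of 1.5 days and 25% at day 60. No search time is added for TAU.

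- Starters-only mean, iRaPID: 0.75 × 1.5 + 0.25 × 60 = 16.1 days, against 14 in TAU. iRaPID looks 2.1 days slower.
- Restricted mean to 180 days, all randomised: iRaPID 0.6 × 16.125 + 0.4 × 180 = 81.7; TAU 0.2 × 14 + 0.8 × 180 = 146.8. iRaPID is 65.1 days shorter.

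Nine late-start patterns were tried (10, 25 or 40% of iRaPID starters late, at day 30, 60 or 90). The starters-only mean reverses in 4 (25 or 40% late, at day 60 or 90) and favours iRaPID in the other 5. The all-randomised restricted mean favours iRaPID in all nine.

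**6. Clock.** A TAU participant who takes s days to reach a provider and 14 more to start has waited s + 14 days since randomisation, but the stated definition records 14. In iRaPID the nurse practitioner's assessment is part of the intervention's first day, so s should be small. The definition therefore removes a delay that iRaPID is meant to shorten.

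**The case against.** The strongest case on the other side has five parts.

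- **These are secondary outcomes in a 50-person pilot.** The primary efficacy outcome, uptake, is defined as current use and is not limited to starters. With visits at 1, 3 and 6 months, it already shows whether more randomised people are on PrEP. This stands, and it lowers the severity.
- **Sign reversal is hypothetical.** A reader might infer that iRaPID will look worse on adherence. The article does not support that. Reversal needs extra starters who adhere less well, and iRaPID's counselling, day 10 contact and day 30 visit could raise adherence among its starters. For time, the same-day design often keeps the sign in iRaPID's favour. This stands: reversal is possible, not predicted.
- **The direction for persistence is unknown.** A reader might infer that late TAU starters, having less follow-up in which to fail, tilt persistence towards TAU. Persistence rests partly on a refill within 30 days of running out. A late starter might have no refill window, be unclassifiable or be counted as a failure, so no direction can be derived.
- **The mixed model does not break randomisation.** This also stands. Conditioning on initiation does that, and for time so does a clock that starts after randomisation. The model is a separate matter of fit.
- **The article is condensed.** Statistical Analyses does not repeat the restriction, and a fuller plan might add an all-randomised analysis or a censoring rule. That is possible, so it cannot be claimed that none exists. But this point rests on what the article states: a population, a model and a clock.

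**Conclusion.** The concern holds for the three secondary PrEP outcomes. As written, they are between-arm efficacy comparisons among people selected by an event after randomisation that iRaPID is designed to change, so randomisation does not protect them.

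The size cannot be fixed from the article. Where extra starters adhere at 30 to 70% against 80% in always-starters, and iRaPID changes nothing in the latter, the starters-only adherence difference runs from −2.5 to −43.8 points while the all-randomised difference stays positive. If both kinds of starter adhere equally, the bias is nil. These results also assume that nobody who would start under TAU fails to start under iRaPID.

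Separately, the repeated-measures model does not fit a once-per-person, censored time, and the stated clock leaves out the TAU search for a provider.

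This should be fixed, but it is not a fatal fault. A reader might infer that the trial's efficacy evidence as a whole is compromised. It is not, because PrEP uptake and MOUD uptake are not restricted to starters.

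**What to change.** 1. Make all randomised participants the population for the between-arm comparison of the three outcomes.
2. Redefine time to PrEP initiation from randomisation to the validated pick-up date, with non-starters censored at 6 months or last contact. Use Kaplan-Meier curves with a log-rank test or a Cox model, stratified by sex as the randomisation was. Remove this outcome from the mixed model.
3. Analyse two binary outcomes at each visit, *on PrEP and adherent* and *on PrEP and persistent*, with non-starters counted as no. The mixed model can serve for these.
4. Keep starters-only adherence and persistence, and time from first provider encounter, as descriptive results, with the number of starters in each arm.

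The cost is small, but it is more than wording: step 2 changes the definition of a stated outcome and should be recorded openly as such. It needs the randomisation date and a last-contact date for non-starters. The article describes no pharmacy check for people who never start, so censoring should not rely on one. The main drawback is that all-randomised adherence and persistence also reflect uptake and partly overlap the primary outcome, which is why the starters-only description stays alongside.

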PrEP is an essential additional tool for people who inject drugs [32,33]. It is not restricted to specially licensed prescribers and reduces HIV transmission from not only drug injection but also sex. Although integrating PrEP into existing evidence-based risk reduction programs can strengthen HIV prevention efforts for people who inject drugs [16,17,19-21,34], its scale-up has been hampered for several reasons. First, PrEP and MOUD each require a separate prescription. They are often delivered in different settings and by clinicians with varying areas of expertise [35], generating excess demands on patients and making access to care more difficult for people who inject drugs. Furthermore, the provision of PrEP and MOUD prescriptions is unnecessarily complex. The traditional PrEP delivery model requires multiple visits before the prescription. Existing data show high attrition rates between initial screening and PrEP initiation, adding to the attrition observed between PrEP referral and initiation [36,37]. The prescription of MOUD also has its own set of demands [38], some of which are regulated by the Drug Enforcement Agency. PrEP and MOUD have been mainly prescribed in a “centralized” care delivery model that focuses more on physicians, is costly, and limits accessibility. There also remains a suboptimal supply of prescribers [39-41], with many physicians reluctant to prescribe medications to people who inject drugs [42-45].

An innovative approach of coprescribing PrEP and MOUD on the same day can streamline delivery, as it addresses impediments to PrEP and MOUD uptake. Same-day PrEP prescription is a safe, feasible, and acceptable approach to linking at-risk individuals to much-needed PrEP care early on [46-48] while decreasing attrition rates between the initial visit and prescription time and increasing adherence [49]. This approach also sets the stage to boost PrEP uptake and makes the current standard of care, which already comprises streamlined access to and initiation of MOUD, more inclusive. The provision of same-day MOUD, when integrated with PrEP, provides the added benefit of stabilizing patients and can therefore strongly complement and facilitate PrEP initiation, adherence, and persistence as has been observed with antiretroviral therapy [34,50]. Additionally, it has the potential to overcome provider-level barriers, increasing the confidence that patients will maintain their treatment regimen [43,45].

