#### Informed Consent, Enrollment, and Randomization

After confirming eligibility criteria and providing informed consent, all participants underwent a baseline assessment, which took approximately 90 minutes and was administered electronically by a trained research staff member in a private room at NHSSP. Participants were then randomized (1:1) to receive either the iRaPID intervention or TAU. Randomization was done via REDCap software (Vanderbilt University), a secure, HIPAA (Health Insurance Portability and Accountability Act)-compliant web app with a built-in randomization feature that allows the development of a defined randomization model. Randomization was stratified by sex to ensure that an equal proportion of participants is present in both arms. Participants are assessed at baseline, and 1-, 3-, and 6-month time points. This approach allows us to examine short-term outcomes and the decay and emergence of intervention effects. Study participants are reimbursed for the time required to complete the assessments (US $35 for the baseline assessment and US $25 for each follow-up assessment).

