#### iRaPID Intervention

The iRaPID program was developed by adapting TAU services for PrEP and MOUD to accommodate same-day coprescription for both medications through a single nurse provider. We used the modified participatory, evidence-based, patient-focused process for advanced practice nursing [61] to guide the optimal use of the NP-led model and refined it to incorporate the same-day coprescription of PrEP and MOUD. Participants randomized to the iRaPID group will receive a prescription for PrEP and MOUD and educational counseling by an NP, followed by safety checks via phone calls or SMS text messages on days 5 and 10; and a clinical visit on day 30 (Figure 1).

During the first day, the NP evaluates the participant's eligibility for PrEP and assesses PrEP readiness. Participants eligible for PrEP are evaluated using the Centers for Disease Control and Prevention's PrEP clinical practice guidelines [62], including acute HIV infection symptoms and laboratory testing for HIV, hepatitis (ie, hepatitis A, B, and C viruses), creatinine, pregnancy (for females), and sexually transmitted infections (ie, gonorrhea, chlamydia, and syphilis). During the same visit, they will also be offered a PrEP prescription for a 30-day supply.

Additionally, the NP assesses MOUD readiness. Participants are screened for buprenorphine maintenance therapy (BMT) eligibility according to the Drug Addiction Treatment Act of 2000 and Treatment Improvement Protocol Series 43 criteria [63]. As methadone maintenance therapy (MMT) is only provided in specialty settings, only BMT is offered at the study site (NHSSP). Patients preferring MMT over BMT are referred to initiate same-day MMT. If the participant is eligible for BMT, a drug toxicology screen is performed, and participants are provided with office or home induction and resources to assist them in self-managing their opioid treatment [64]. The resources provided include a home induction kit with an instruction sheet, BMT film packets, nonsteroidal anti-inflammatory drugs (for body pain), hydroxyzine (for anxiety and insomnia), and loperamide (for diarrhea). Additionally, patients receive adherence and potential medical adverse events counseling.

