## Discussion

### Principal Findings and Implications

This ongoing trial aims to test an NP-led integrated HIV prevention program for people who inject drugs that combines same-day coprescribing of PrEP and MOUD. This strategy addresses delayed initiation and low linkage to HIV prevention (PrEP) and substance use (MOUD) care in traditional models. We hypothesize that the iRaPID intervention will be feasible and acceptable among people who inject drugs and will prove to be more efficacious than the standard of care for PrEP and MOUD services. We also anticipate that the results and qualitative feedback from participants and stakeholders will inform the refinement of the iRaPID intervention for a future large-scale RCT.

Same-day access to HIV preventive care may be particularly crucial for people who inject drugs with MOUD as they remain a hard-to-reach group and have significantly higher rates of attrition and poor linkage to care. Since HIV acquisition risk persists during delays, timely PrEP and MOUD initiation are critical in at-risk populations. Individuals with streamlined care initiation may also experience enhanced self-efficacy, encouraging continued engagement. Hence, our results could impact local and international PrEP and MOUD scale-up policies and promote engagement in HIV prevention services.

Given the risk of continued HIV outbreaks amidst the ongoing opioid crisis, scaling up PrEP alongside MOUD for people who inject drugs is crucial for HIV prevention. If successful, subsequent stand-alone tailored programs can be developed to support communities where opioid use is high and HIV outbreaks are likely, thereby promoting a transition to integrative care. Considering the limited access to and scale-up of harm-reduction strategies among people who inject drugs and the existing multilevel barriers to PrEP uptake, effective interventions are urgently needed to fill this critical gap. Given the significant growth in the waivered NP workforce, trained nurses are ideally situated to deliver this integrated care model. The iRaPID program represents a paradigm shift in HIV prevention and may be a particularly crucial strategy for people who inject drugs with OUD, as they remain an easy-to-miss subgroup with high rates of loss to follow-up and poor linkage to care.

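### Time to PrEP initiation starts at the first provider encounter and covers initiators only, so TAU's wait to reach a provider is left out of the between-arm comparison

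*Protocol article*

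**What the plan says.** All references are to the protocol article.

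- **Outcome definition (Outcome Measures).** Time to PrEP initiation is a secondary outcome, obtained by "recording the number of days between the first encounter with the NP or health care provider and the day of initiation of PrEP", with the initiation date validated by pharmacy pick-up.
- **Population (Outcome Measures).** It is restricted to initiators: "For those who initiate PrEP, we will also evaluate the time to PrEP initiation".
- **Randomisation (Informed Consent, Enrollment, and Randomization).** After the baseline assessment, "Participants were then randomized (1:1) to receive either the iRaPID intervention or TAU".
- **iRaPID route (iRaPID Intervention).** The study nurse practitioner assesses PrEP eligibility on the first day. "During the same visit, they will also be offered a PrEP prescription for a 30-day supply".
- **TAU route (Treatment as Usual).** "They are provided with a comprehensive list of PrEP and MOUD programs available in the area". Two PrEP appointments generally follow: "During the second visit, which usually occurs 1 to 3 weeks later", and the prescription is given then.
- **Analysis (Statistical Analyses).** The outcome is among those used to test whether iRaPID does better than TAU. It is to be handled like the other outcomes, for which the section describes a generalised linear mixed model.
- **Purpose (Principal Findings and Implications).** "This strategy addresses delayed initiation and low linkage to HIV prevention (PrEP) and substance use (MOUD) care in traditional models".

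**The concern.** A randomised comparison of times needs the same starting point in both arms, normally randomisation. Here the starting point is an event after randomisation whose timing depends on the assigned arm. In iRaPID the first provider is the study nurse practitioner and the encounter belongs to the intervention's first day. In TAU the participant has to locate and reach a provider, and the clock does not run while that happens.

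A TAU participant who takes 60 days to reach a clinic and gets a prescription 14 days later scores the same as one who reached it at once. The outcome therefore cannot register the linkage part of the delay, although the article names low linkage as something the program addresses. Because the pilot's estimates are meant to inform a future RCT, a distorted time-to-initiation contrast would carry over into that design.

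The initiators-only restriction is a second, separate problem. It conditions the comparison on a post-randomisation outcome that the intervention is intended to change, so the two groups compared are no longer the randomised groups.

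**Working it through.** The article states no effect size, event count or power for this outcome, so there is no figure to reproduce. The check concerns what the stated clock counts.

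**Inputs**
- G, TAU first visit to prescription: 7 to 21 days (Treatment as Usual, 1 to 3 weeks); midpoint 14.
- iRaPID first visit to prescription offer: 0 days (iRaPID Intervention).
- L, TAU randomisation to first provider: not given. Assumed at 0, 7, 14, 30 and 60 days.
- TAU arm size: about 25 (50 participants, 1:1).

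**Step 1: what each clock records for TAU, counted to prescription**

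Stated clock = G. Clock from randomisation = L + G. Share hidden = L / (L + G).

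| L (assumed, days) | Stated clock, G = 14 | From randomisation, G = 14 | Share hidden, G = 14 | Share hidden, G = 21 to G = 7 |
|---|---|---|---|---|
| 0 | 14 | 14 | 0/14 = 0% | 0% to 0% |
| 7 | 14 | 21 | 7/21 = 33% | 25% to 50% |
| 14 | 14 | 28 | 14/28 = 50% | 40% to 67% |
| 30 | 14 | 44 | 30/44 = 68% | 59% to 81% |
| 60 | 14 | 74 | 60/74 = 81% | 74% to 90% |

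The outcome ends at pick-up, not prescription. Any days between the two enlarge the denominator and lower these shares. For example, with L = 30, G = 14 and an assumed 7 days to pick-up, the share is 30/(30 + 14 + 7) = 30/51 = 59%.

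**Step 2: letting L vary between people**

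A simulation took L as exponential, G as uniform on 7 to 21 days, and a 180-day window. These distributional forms are also assumptions.

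| Mean L (assumed, days) | Mean among TAU initiators, stated clock | Mean among TAU initiators, from randomisation |
|---|---|---|
| 14 | 14.0 | 28.0 |
| 30 | 14.0 | 43.4 |
| 60 | 14.0 | 62.8 |
| 120 | 14.0 | 78.4 |

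The stated measure does not move as linkage gets slower. That follows from the definition and does not depend on the values chosen for L.

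**Step 3: the initiators-only restriction**

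If a fraction q of about 25 TAU participants never reach a provider (assumed), 25q drop out of the comparison: 5, 10 or 15 at q = 20%, 40% or 60%, leaving at most 20, 15 or 10. Moving the origin to randomisation does not bring them back while the restriction stands, because someone who never reaches a prescriber does not initiate. Both features have to change.

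**The case against.** The strongest defence is that the interval from first provider to pick-up is a coherent measure of a central mechanism of iRaPID: replacing a two-visit PrEP pathway with a same-day prescription. This stands. The 1 to 3 week gap between TAU visits lies wholly inside the stated clock. A reader might infer that the outcome misses the whole delay iRaPID is built to remove; it misses only the segment before the first provider.

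A reader might also infer that the choice of origin is what leaves never-linked TAU participants without a value. The documents do not support that, because the initiators-only restriction already excludes them under any origin. Nor are they lost to the trial, since they count as non-uptake in the primary outcome.

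The Introduction is weaker support than it may look. Its phrase "adding to the attrition observed between PrEP referral and initiation" concerns people lost, not days elapsed, and is one of several reasons listed. The sentence on linkage in Principal Findings and Implications is the better support.

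Finally, the size is hypothetical. Table 1 places TAU PrEP steps on the study timeline, with a footnote putting the exact day at usually 3 to 7 days after baseline, depending on laboratory results. Its columns are broken in the available text and Treatment as Usual describes self-directed access, so the table does not settle the matter. It is a reason to keep short linkage times in the range. If TAU encounters did occur at baseline, starting at randomisation would change nothing.

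**Conclusion.** The point holds as a definition problem in a secondary outcome and should be fixed. The two arms are timed from different origins in an outcome the article compares between arms, and the time left out falls essentially on TAU.

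The size cannot be determined from the article. Over assumed linkage times of 0 to 60 days, with a 14-day visit gap and counting to prescription, the hidden share of the TAU delay runs from 0% to 81%; counting to pick-up lowers it. It would be wrong to infer that most of the delay is certainly hidden.

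Omitting the linkage wait understates any iRaPID advantage on this outcome. The net direction is less certain, because selection to initiators could push the comparison either way. It would also be too strong to say that the trial's main conclusion is compromised: primary uptake does not use this clock, and this is a 50-person pilot aimed at feasibility, acceptability and preliminary estimates.

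**What to change.** - **Definition.** Define time to PrEP initiation as days from randomisation to first pharmacy-verified PrEP pick-up.
- **Population.** Include every randomised participant in the assigned arm, and drop the restriction to initiators for this comparison.
- **Censoring.** Censor non-initiators at 6 months or last follow-up.
- **Analysis.** Replace the mixed model for this outcome with a time-to-event method, for example Kaplan-Meier curves with a log-rank test or a Cox model, stratified by sex as the randomisation was.
- **Retain.** Report days from first provider encounter to pick-up among initiators as a descriptive process measure, labelled as not a randomised comparison.

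The cost is small but is more than a change of wording: the origin, the population and the analysis method all change for this outcome. No new data should be needed, since randomisation was done in REDCap and pharmacy pick-up dates are already planned. When the article was published, data collection was still due to run to February 2023, which left time to settle the definition before analysis.
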